### Outcomes

The primary outcome will be functional limitations, as measured with the Pain Interference subscale of the Brief Pain Inventory – Short Form (BPI). The secondary outcomes will include pain severity as measured with the Pain Severity subscale of the BPI, and health-related quality of life as measured with the EQ-5D-5L. As pain-related fear has been shown to influence outcomes in military members and conservative management reduces pain-related fears [20, 46], both interventions will also be compared on their impact on pain-related fears, measured with the Tampa Scale for Kinesiophobia (TSK) [38]. Furthermore, region-specific symptoms and functional limitations will be assessed using the Oswestry Disability Index (ODI) for low back pain, the shortened version of the Disabilities of the Arm, Shoulder and Hand (*Quick*DASH) for rotator cuff-related shoulder pain, Knee Outcome Survey Activities of Daily Living Scale (KOS-ADLS) for patellofemoral pain syndrome and Lower Extremity Functional Scale (LEFS) for lateral ankle sprain. To monitor compliance with home exercises, participants will be asked to maintain a weekly web-based logbook on RedCap during the 12 weeks of the intervention. Finally, participant’s satisfaction with treatment will be assessed at the end of the treatment (i.e., week-12) (see bellow for further description).

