### Satisfaction

Patients satisfaction with treatment will be assessed at 6 and 12 weeks using the Patient Acceptable Symptom State (PASS) [62, 63], It asks patients weither they are satisfied with their current state or not and to rate their satisfaction on a 0–10 numeric scale (0 representing not satisfied at all, and 10 very much satisfied) [49]. They will also be asked to rate their satisfaction with treatment received using a three-item Likert scale (“not satisfied”, “satisfied” or “very much satisfied”), their satisfaction with the frequence of treatments (“not enough”, “just right” or “too much”), their satisfaction with the duration of treatments (“too short”, “long enough”or “too long”) and their satisfaction with the time spent with the PT during the treatments (“not enough”, “just right” or “too much”) [49, 51, 64].

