### Statistical analyses

Descriptive statistics will be used for all outcome variables at each measurement time to summarise results. Baseline demographic data will be compared (independent *t*-tests and Chi-squared tests) to establish the comparability of groups. An intention-to-treat analysis will be used in which all participants will be analysed in the group to which they were assigned. In addition, sensitivity analyses will also be performed using per-protocol analyses; these analyses will allow to verify the consistency of the results in participants strongly compliant with the interventions (e.g., 75% attendance and home exercises). All dropouts and the reason for dropping out of the study will be reported. Any harm or unintended effects and co-interventions will be recorded. A 2-way ANOVA (2 Interventions [Group-Based or UPC] × 4 Times [0, 6, 12, 26 weeks]) will be used to analyse and compare the effects of the interventions on the primary outcome (Pain Interference Scale) and on four of the secondary outcomes (Pain intensity subscale, EQ-5D-5L, TSK) (SPSS, proc. GENLIN [Generalized Estimating Equations – GEEs]). Effect sizes (Cohen’s *d* for between-groups comparisons, Glass’s Δ for within-group comparisons) will be calculated. Nonparametric Analysis for Longitudinal Data (nparLD Package 2.1, R-software, v.3.6.1) will also be considered in cases where GEEs are not applicable (undefined distributions). If nparLD are used, effect sizes will be reported as relative treatment effect. Satisfaction with treatment will be compared between the two interventions using Chi-squared test for the PASS and Mann Whitney test or independent *t*-tests for satisfaction questions using the Likert scales. Exploratory analyses (using a similar statistical approach as for primary outcome) will be performed to compare the two interventions for each of the four conditions using the region-specific questionnaires (ODI, KOS-ADLS, *Quick*DASH, LEFS).

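### Mann-Whitney or t-tests on the three satisfaction items whose best answer is in the middle compare the direction of complaint, not satisfaction; the assessment time is also inconsistent

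*Protocol article*

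**What the plan says.** The Satisfaction section of the protocol article describes the PASS, a 0–10 rating and four categorical questions. One question, on the treatment received, runs in order from *not satisfied* to *very much satisfied*. The other three are:

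- The item on how often treatment was given: "their satisfaction with the frequence of treatments (“not enough”, “just right” or “too much"
- The item on how long treatment lasted: "their satisfaction with the duration of treatments (“too short”, “long enough”or “too long"
- The item on therapist time: "their satisfaction with the time spent with the PT during the treatments (“not enough”, “just right” or “too much"

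The Statistical analyses section gives the rule: "Satisfaction with treatment will be compared between the two interventions using Chi-squared test for the PASS and Mann Whitney test or independent". That sentence ends by offering the t-test as the alternative to Mann-Whitney, and the pair is meant "for satisfaction questions using the Likert scales". It names no recoding and no separate test for the three items above.

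On timing, the Outcomes section says "satisfaction with treatment will be assessed at the end of the treatment (i.e., week-12", and the Abstract also places the assessment at the end of the intervention. The Satisfaction section says "satisfaction with treatment will be assessed at 6 and 12 weeks using the Patient Acceptable Symptom State (PASS". The Statistical analyses section does not say at which visit the arms are compared.

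**The concern.** In the three items on frequency, duration and time with the physiotherapist, the satisfied participant picks the middle category. Both ends express dissatisfaction, for opposite reasons. A rank test or t-test orders the answers low, middle, high, so a complaint of too little in one participant offsets a complaint of too much in another. The quantity tested is then the net direction of complaint, although the article introduces each item as a measure of satisfaction.

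Satisfaction is a stated secondary objective, with the hypothesis that participants will be equally satisfied in both arms. A test on the wrong scale can miss a real difference in dissatisfaction. It can also report a difference where the same share of each arm is dissatisfied. Either result would be misread if presented as a satisfaction result.

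**Working it through.** **Inputs from the article.** 60 per arm and 15% expected loss (Sample size), so 60 × 0.85 = 51 per arm. The plan gives no figure for satisfaction to reproduce. The response distributions below are therefore assumptions, written as percentages low/middle/high.

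**What the tests measure.** Code the answers 1, 2, 3 with probabilities p1, p2, p3. The mean is 2 + (p3 − p1), so the t-test compares p3 − p1 between arms. With probabilities a in one arm and b in the other, Mann-Whitney depends on

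P(A>B) − P(A<B) = a2(b1 − b3) + (a3 − a1)b2 + a3b1 − a1b3.

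This is zero whenever a1 = a3 and b1 = b3, however different a2 and b2 are. The share satisfied is p2, which neither test targets.

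**Worked example, 60 per arm: dissatisfaction differs.** Counts 12/36/12 v 3/54/3 (24/60 = 40% v 6/60 = 10% dissatisfied).

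- Both means are 2.00, and U = 1800 = 60 × 60/2. Mann-Whitney p = 1.00 and t-test p = 1.00.
- Three-category chi-squared: expected counts 7.5/45/7.5 per arm; 4 × 4.5²/7.5 + 2 × 9²/45 = 10.8 + 3.6 = 14.4 on 2 df, p = 0.0007.
- Middle v not: 2 × 9²/45 + 2 × 9²/15 = 3.6 + 10.8 = 14.4 on 1 df, p = 0.00015.

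**Converse example: dissatisfaction is equal.** Counts 15/42/3 v 3/42/15 (18/60 = 30% dissatisfied in each arm). The means are 108/60 = 1.80 and 132/60 = 2.20. Mann-Whitney p = 0.00007 and t-test p = 0.00004, although the share satisfied is identical.

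**Rejection rates by simulation, 51 per arm, two-sided 0.05.** Ranges show the spread between repeated runs.

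| Assumed pattern | Dissatisfied | Means | Mann-Whitney | t-test | Middle v not |
|---|---|---|---|---|---|
| 10/80/10 v 25/50/25 | 20% v 50% | 2.00 v 2.00 | 0.06 | 0.05 | 0.90–0.91 |
| 5/90/5 v 20/60/20 | 10% v 40% | 2.00 v 2.00 | 0.06–0.07 | 0.05 | 0.95–0.96 |
| 5/90/5 v 30/40/30 | 10% v 60% | 2.00 v 2.00 | 0.08 | 0.05 | 1.00 |
| 20/80/0 v 35/50/15 | 20% v 50% | 1.80 v 1.80 | 0.07 | 0.05 | 0.90 |
| 5/90/5 v 30/60/10 | 10% v 40% | 2.00 v 1.80 | 0.58–0.60 | 0.54–0.55 | 0.95–0.96 |
| 10/90/0 v 40/60/0 | 10% v 40% | 1.90 v 1.60 | 0.96 | 0.96 | 0.96 |
| 5/70/25 v 25/70/5 | 30% v 30% | 2.20 v 1.80 | 0.97–0.98 | 0.98 | 0.04–0.05 |

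Two further cases in which all the extra complaints go one way, Mann-Whitney v middle-or-not: 5/90/5 v 35/60/5 gives 0.93 v 0.96, and 10/85/5 v 35/60/5 gives 0.77 v 0.83.

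The three-category chi-squared test rejects 0.91 for 5/90/5 v 20/60/20, 0.94 for 5/90/5 v 30/60/10 and 0.95 for 5/70/25 v 25/70/5. It responds both to a difference in satisfaction and to a difference in direction.

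**The case against.** **Size of the loss.** The near-total loss of power occurs only where the extra complaints split about equally between the two ends; in the first four rows of the table the mean scores are identical. With 5 to 20 participants per therapist in the group arm (Group-based supervised training program), the natural extra complaint about therapist time is that there is too little. That is one-way, and the planned tests would detect it. This stands: a reader might infer that the planned tests are built to show no difference, or would falsely confirm equal satisfaction, and the documents support neither reading. The PASS, the 0–10 rating and the ordered item are unaffected. Reading a non-significant result as equality is a separate matter that no choice of test here would cure.

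**Where the arms should differ.** A reader might also infer that these three items are where the arms should differ most. The article does not say so. Its Interventions section gives both arms the same maximum number and length of sessions.

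**The alternative has its own gap.** Comparing only the middle answer with the rest misses direction altogether (0.04–0.05 in the last row of the table), and whether patients want more or less therapist time is a fair question. This stands and shapes the fix.

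**Wording and detail.** The article attaches the Likert label by name only to the ordered item. On a narrow reading the other three have no stated test; the plural wording in Statistical analyses favours the reading that they are included. Descriptive statistics are promised for all outcomes, so the category counts would probably be visible. Item coding may also sit in an analysis plan that is not shown. None of this removes the point: the article states a test, and for these items it is aimed at the wrong quantity.

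**Conclusion.** The concern holds in a limited form. For three single items within a secondary outcome, the stated tests compare the direction of complaint instead of satisfaction. The consequence depends on a response pattern that cannot be known in advance. Rejection is 5% to 8% when extra complaints balance, about 0.58 against 0.96 when they partly balance, and close to the alternative when they go one way. It is about 98% when dissatisfaction is equal but opposite in direction. These rates rest on assumed distributions, 51 per arm and a two-sided 0.05 level; the mismatch between test and quantity does not depend on them. The primary analysis and the sample size are untouched.

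The timing inconsistency (week 12 only, against weeks 6 and 12) is a separate and certain contradiction. It leaves open which visit, or visits, the satisfaction comparison uses.

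**What to change.** In Statistical analyses, treat the frequency, duration and therapist-time items separately. As the satisfaction comparison, compare the proportion answering *just right* or *long enough* between arms, as a difference with 95% CI and a chi-squared or Fisher test. Beside it, report the 2×3 table with a three-category chi-squared test, so that direction of complaint is still tested. Keep Mann-Whitney for the ordered treatment-satisfaction item.

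Reconcile the Outcomes and Satisfaction sections on when satisfaction is assessed, and state at which visit or visits the arms are compared.

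The cost is a sentence or two of wording. The raw categories are already to be collected, so no new data or participants are needed.

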### Sample size

Based on our sample size calculation, calculated for our primary outcome (Pain Interference subscale of the Brief Pain Inventory) using data from a pilot study on military members with MSKd [33], 15 participants per diagnosis will be required per group for a total of 120 participants (60 participants/group) (G*Power 3.1.7; α = 0.05, 1-β = 0.95, Baseline mean: 2.9+/− 1.5 points, Follow-up mean: 0.8+/− 1.2 points, expected lost at follow-up = 15% [based on past experiences with this population]. This number will enable us to determine the effects of the interventions for each of the four conditions.

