#### Group-based supervised training program

The low back pain, upper extremity and lower extrimity Training Programs were developed for military members with MSKd by the Valcartier Health Centre PTs based on a literature review and clinical experience [20, 21]. These group-based training programs have been implemented and used for several years in addition to individual physiotherapy to increase the number of patients managed. They are composed of stations that each include several exercices of varying levels of difficulty (see further description below). Group size will vary between 5 to 20 participants for one PT or PT technologist, and each military member performs his/her own exercices. For example, during a typical session, the participant and PT will choose one exercise to perform per station according to two main criteria: severity of the condition (i.e., symptoms and limitations) and the ability to perform the exercises optimally. The level of supervision will be adapted to the participant’s needs and performance. Exercises are progressed if the quality of movement control is considered adequate by the PT and the exercise is no longer a challenge according to the participant. Exercise parameters and progressions of the programs have been chosen to increase strength, endurance and neuromuscular control [39, 40]. Progression in the programs leads to the execution of exercises that simulate functional and occupational tasks (task-oriented approach with gradual exposure) [21]. In accordance with recognized motor learning principles, participants will be encouraged to complete a large variety of exercises and to focus on the quality, rather than the quantity of their movements [41]. Exercises will be paused if pain is greater than 3/10 during execution or if fatigue results in compensatory movements [42].

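### The 2 × 4 GEE names no therapist or exercise-group term although one arm is treated in groups, and its exploratory use within each condition would need small-sample inference

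*Protocol article*

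**What the plan says.** The Statistical analyses section of the protocol article sets out a two-factor model, intervention (2) by time (4: weeks 0, 6, 12, 26), for the primary outcome and several secondary ones. The software reference is "SPSS, proc. GENLIN [Generalized Estimating Equations". It names no covariance estimator, working correlation or reference distribution, and no factor for therapist or exercise group. For the region-specific questionnaires within each condition it adds: "Exploratory analyses (using a similar statistical approach as for primary outcome) will be performed".

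On delivery, the Group-based supervised training program section says: "Group size will vary between 5 to 20 participants for one PT or PT technologist". Randomisation/blinding states that the two interventions are given by different physiotherapists, so therapists are nested within arm.

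The Sample size section states that "15 participants per diagnosis will be required per group", 120 in total, and that this number is meant to show effects in each of the four conditions. It contains no design effect for grouped delivery.

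**The concern.** Two separate features bear on the standard errors and tests.

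1. **Shared delivery.** Soldiers in the group arm share a supervisor, who helps choose exercises, judges progression and decides when treatment can stop. Their outcomes may therefore be correlated. A model whose only factors are arm and time, with the soldier as the independent unit, leaves that correlation out of the between-arm variance. This reaches the primary analysis. It matters here because the Background hypothesises that group care does no worse than individual care: an interval that is too narrow rules out inferiority too easily, besides raising the false-positive rate.

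2. **Few participants per condition.** Carrying the same approach into each condition leaves about 13 per arm. GEE inference in its basic form (sandwich covariance, chi-square reference) relies on large numbers of independent units. These analyses are labelled exploratory, but the trial was sized by condition and readers interested in one programme will look at them.

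**Working it through.** **The plan's own sample size.** Inputs from Sample size: "α = 0.05, 1-β = 0.95"; "Baseline mean: 2.9+/− 1.5 points"; "Follow-up mean: 0.8+/− 1.2 points"; loss 15%.
- Pooled SD = √((1.5² + 1.2²)/2) = 1.358; d = (2.9 − 0.8)/1.358 = 1.546.
- A two-sided two-sample t-test (noncentral t) needs 12 per group (power 0.951; 11 gives 0.931).
- 12/(1 − 0.15) = 14.1, rounded up to 15.

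The stated 15 is reproduced with no design effect in it. After 15% loss, 30 per condition leaves 25.5 (about 13 per arm) and 120 leaves 102 (51 per arm).

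**Clustering.** Assumptions: m = 10 trial participants per therapist or group; ICC 0.01 to 0.05; clustering in the group arm only; equal arm sizes. None of these is in the article except the session size of 5 to 20.
- Variance ratio R = ([1 + (m − 1)·ICC] + 1)/2.
- True two-sided level = 2·[1 − Φ(1.96/√R)].

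| ICC | m | R | √R | true level |
|---|---|---|---|---|
| 0.01 | 10 | 1.045 | 1.022 | 5.5% |
| 0.05 | 5 | 1.100 | 1.049 | 6.2% |
| 0.05 | 10 | 1.225 | 1.107 | 7.7% |
| 0.05 | 20 | 1.475 | 1.214 | 10.7% |

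A simulation of the week-12 change contrast at 51 per arm (within-person correlation 0.5, normal complete data, uncorrected sandwich) gives 6.6%, 8.3% and 10.9% for ICC 0.05 with m = 5, 10 and 20, and 5.6% without clustering. With a t reference in place of the normal, the m = 10 figure is 7.7%, equal to the closed form.

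**Small samples, conditional on an uncorrected sandwich and a chi-square reference.** With complete normal data and a saturated arm-by-time mean, the sandwich covariance is (n − 1)/n times the unbiased one, and the 3-df Wald statistic is a multiple of Hotelling's T². With ν = 2(n − 1), T²·(ν − 2)/(3ν) follows F(3, ν − 2). The chi-square critical value on 3 df is 7.815.
- n = 13 (ν = 24), interaction: 7.815 × (12/13) × 22/72 = 2.204; P(F(3,22) > 2.204) = 11.6%. Simulation: 11.7%.
- n = 13, one contrast: 1.96 × √(12/13) = 1.883; P(|t₂₄| > 1.883) = 7.2%. Simulations: 7.1 to 7.3%.
- n = 51 (ν = 100), interaction: 7.815 × (50/51) × 98/300 = 2.503; P(F(3,98) > 2.503) = 6.4%. Simulations: 6.3 to 6.5%.
- n = 51, one contrast: 1.96 × √(50/51) = 1.941; P(|t₁₀₀| > 1.941) = 5.5%.

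**Where the small-sample inflation comes from.** The standard error is short by only 1 − √(12/13) = 3.9% at 13 per arm and 1 − √(50/51) = 1.0% at 51. With the covariance made unbiased but chi-square kept, the interaction at n = 13 still rejects 9.6% of the time: 7.815 × 22/72 = 2.388 on F(3,22). So most of the excess comes from the reference distribution. In the simulation, a small-sample correction with an F or t reference returns the rates to 5.0% and 4.8%.

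**The case against.** The strongest reply is that much of this rests on things the article does not say.

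- **Robust errors.** A reader might infer from the mention of GEE in SPSS that uncorrected robust errors are used. The article names no covariance estimator, reference distribution or correction, and such settings commonly go to an analysis plan. The small-sample figures are therefore conditional.
- **Certainty about clustering.** A reader might conclude that the standard errors will be too small. No ICC, number of therapists or number of groups is given. Each soldier does his or her own exercises and has an individualised home programme, which may keep the ICC low. The 5 to 20 is session size, not stated to be all trial participants, and recruitment is consecutive across three programmes. At ICC 0.01 the effect is negligible.
- **Missing data.** It is tempting to add that GEE is valid only if loss is unrelated to earlier outcomes. That is too absolute: for a Gaussian outcome with a saturated mean and a correctly specified working correlation, the estimates can be consistent when loss depends on observed outcomes. The working correlation is not fixed in the article, so no finding follows.
- **Status.** The per-condition comparisons are exploratory.

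All four limits stand. They do not remove the clustering point. The article lists the factors in the model and the inputs to the sample size, and neither allows for grouped delivery. Individual exercises under a shared supervisor can make the ICC small but do not make it zero. Counting the group arm alone also leaves out patients in individual care who share a therapist.

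**Conclusion.** The point holds in conditional form.

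- **Primary analysis:** the stated 2 × 4 model names no therapist or group term while one arm is delivered in groups by arm-specific therapists. Any positive ICC understates the between-arm standard error. With the assumed ICC of 0.01 to 0.05 and 10 per cluster in the group arm, the true level is about 5.5 to 7.7% instead of 5%: negligible at the bottom of the range, worth handling at the top.
- **Per-condition analyses:** if they use an uncorrected robust covariance with Wald chi-square tests, type I error is about 12% for the 3-df interaction and 7% for a single contrast. Under the same condition the pooled primary analysis is little affected, at about 6.3% and 5.5%. This is mainly a fault of the reference distribution, since the standard error itself is only about 4% short.

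The figures assume normal outcomes; the small-sample ones also assume complete data, and the simulations a within-person correlation of 0.5. The article supplies the session size, loss rate and sample size; the ICC and the number of trial participants per cluster are assumptions.

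**What to change.** 1. Record the supervising therapist and the exercise group for every participant during the trial, since this may not be recoverable afterwards.
2. Account for it in the primary model with a random effect for therapist or group in the group arm, and report the ICC. With 51 participants in clusters of 10 there would be only about five clusters, so the effect may not be estimable. In that case report a sensitivity analysis over ICC 0.01 to 0.05.
3. For the per-condition comparisons, name a small-sample method: for example a repeated-measures mixed model with Satterthwaite or Kenward-Roger degrees of freedom, or a bias-corrected GEE with a t or F reference. A bias correction alone, with chi-square kept, is not enough for the interaction.

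The cost is one extra recorded field, revised analysis wording and somewhat wider intervals. Under the assumptions above, allowing for clustering widens the primary interval by about 2 to 11% (√1.045 to √1.225). At 13 per arm, replacing an uncorrected sandwich and normal reference by a corrected one with t widens a single-contrast interval by about 10%: 2.064/(1.96 × √(12/13)) = 1.096.
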